
#### TCM pattern

Five typical symptoms for LSSD are assessed to evaluate the changes of TCM Pattern, involving: (i) abdominal distension, (ii) borborygmus and flatus, (iii) distension and fullness in chest and hypochondrium, (iv) frequent sighing, poor appetite, and (v) mental depression or irritability. Investigators will grade the TCM pattern scale (None = 0, Mild = 1, Moderate = 2, Severe = 3) as shown in Additional file 3: Table S2. Efficacy assessment standards of Syndrome of Chinese medicine are as follows: Clinical remission: clinical symptoms and signs disappear or basically disappear, total scoring declining ≥ 95%; Excellence: clinical symptoms and signs are significantly improved, total scoring declining ≥ 70%; Effective: clinical symptoms and signs are improved, total scoring declining ≥ 30%; Invalid: clinical symptoms and signs are without obvious improvement or even with exacerbation, total scoring declining < 30%. The effective rate on TCM pattern will be evaluated with following calculation formula (nimodipine method): [(total score of prior treatment − total score of post treatment)/total score of prior treatment] × 100% [23].

#### Irritable bowel syndrome-quality of life

The health-related quality of life of participants will be measured with validated Irritable Bowel Syndrome-Quality of Life (IBS-QoL) questionnaire, which includes 34 items and involves eight aspects: dysphoria (Q1), interference with activity (Q2), body image (Q3), health worry (Q4), food avoidance (Q5), social reaction (Q6), sexual (Q7) and relationship (Q8) [27]. Each item will be rated on a 5-point Likert scale. Higher score reflects better quality of life. The difference of score before and after the medication will be evaluated.

#### Irritable bowel syndrome-symptom severity score

The IBS-SSS questionnaire will be completed at visit 2, 3, 4, 5. The IBS-SSS involves five aspects that measures on the severity of abdominal pain, the frequency of abdominal pain, the severity of abdominal discomfort, defecation satisfaction, and interference with daily life. The range of score is 0–500 points scale [28]. The change of score before and after the medication will be evaluated.

### Safety outcome

In this study, adverse events (AEs) or SAEs related to IMPs are used for safety evaluation, including new incurrence symptoms or diseases, abnormal vital signs, clinically significant abnormal laboratory examination on renal or liver function. The severity of AEs is graded based on the Common Terminology Criteria for Adverse Events v4.0.

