## Objective

The major objectives of this study are as follows: (1) investigate the efficacy of the Chinese medicine JCM-16021 for IBS-D participants with LSSD pattern of TCM; and (2) assess the safety of the Chinese medicine JCM-16021.

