### Blinding

The trial is a double-blinded design, in which all the Chinese medicine practitioners, research assistants and participants are ignorant of the treatment assignments. The physical appearance of placebo is consistent with the Chinese medicine JCM-16021, including the packaging, appearance, color and taste. Pharmaceutical company will be responsible for labelling the Chinese medicine JCM-16021 and placebo according to the blinding codes. ‘16021A’ and ‘16021B’ will be used to label the interventions. The blinding code will be kept strictly confidential by the principal investigators until completion of the final statistical analysis and report of the trial. Only if there is a serious adverse event (SAE) relevant to the research medication, the assignment code will be broken. The date and reason for breaking the blinding code should be recorded in the case report form (CRF). Relevant institutions, including the Research Ethics Committee of Hong Kong Baptist University and Department of Health of Hong Kong Special Administrative Region should be informed accordingly within 24 h.

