### Data collection, management and monitoring

All data will be collected through patient diaries, questionnaires, and CRFs. All enrolled participants have to record their abdominal pain, stool frequency, stool consistency in a paper-based patient diary throughout 18 weeks of study. At each visit, participants will be required to return the diaries and complete some questionnaires, including the GAI questionnaire, the IBS-QoL questionnaire, and the IBS-SSS questionnaire. Chinese medicine practitioners and study coordinators have to fill in the CRFs to record relevant information, such as blood pressure, the changes of TCM Pattern, and compliance/noncompliance with research medication and concomitant conventional maintenance therapy, etc. These data collected in visit 2 will be the baseline data. All personal information of participants will be kept confidential. The Research Electronic Data Capture (REDCap) [29, 30] will be used to collect and manage all participants’ data by researchers. All centers have corresponding personnel to input the data timely. The researchers with authorized accounts can log in and browse the data. All raw data collected by patient diaries, questionnaires, and CRFs could be shared based on the request and special approval from the team. During the whole study, all AEs (new incurrence symptoms or diseases, abnormal vital signs, clinically significant abnormal laboratory examination) should be recorded in CRF and investigators are also required to fill in the relevant information in the “Adverse Event Report Form”, which includes start time, duration, severity, and relationship with IMP etc. Once there is an AE which results in hypersensitivity towards research medication or significant abnormality on liver or renal function, investigators can suspend or terminate the IMP, and report to principal investigators in time. If there are any SAEs, investigators should fill in the “Serious Adverse Event Report Form” with signature and report to the Research Ethics Committee within 24 h. Also, all AEs and SAEs are required to be reported to the Department of Health of Hong Kong Special Administrative Region every year. The trial document will be kept for 7 years after the completion of the trial. The Research Ethics Committee of Hong Kong Baptist University and the Department of Health of Hong Kong Special Administrative Region play a role to monitor the data. The principal investigators need to submit the progress reports to the Research Ethics Committee of Hong Kong Baptist University and the Department of Health of Hong Kong Special Administrative Region every year, and to the funding agency Innovative Technology Commission of the Government of Hong Kong Special Administrative Region at every 6 months.

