### Statistical analysis

Baseline data will be descriptively summarized. Categorical variables will be summarized by frequencies and percentages. Continuous variables will be summarized with mean and standard deviation [mean ± SD].

For the outcome analysis, comparisons between two groups for continuous variables will be conducted by using an analysis of variance (ANOVA), with other confounding factors like a multicenter character conducting the covariate analysis. Statistical analysis for the data which do not meet above conditions (e.g., non-normal) will be conducted with the use of non-parametric test. Categorical data of different groups will be reported as frequency (proportion). Comparisons between groups for these categorical data will be assessed with the use of chi-square test (CMH test) or non-parametric testing. For the repeatedly measured outcomes, the difference with the baseline data (follow-up minus the baseline) will be analyzed and the baseline data will be included in the model as covariables. Subgroup analyses will be carried out irrespective of whether there is a significant treatment effect on the primary outcome. The participants’ drop-out will be descriptively summarized. Both per-protocol analysis (PP) and intention-to-treat (ITT) analysis will be used to conduct the efficacy analysis. All treatment groups’ comparisons except for the primary outcome will be performed at a two-sided level of 0.05.

The safety analysis will mainly be performed by analysis of the incidence of adverse events between groups and the incidence of abnormal laboratory data before and after treatment between groups. A detailed description of the statistical analysis plan (SAP) is provided in Additional file 3.

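### The safety outcome is worded as drug-related events only, which conflicts with the protocol's own rules for recording and comparing all adverse events

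*Protocol article*

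**What the plan says.** Safety is the second of two major objectives; the Objective section undertakes to "assess the safety of the Chinese medicine JCM-16021".

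Three places in the protocol article bear on which events count:

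- **Safety outcome**, the only definition of the outcome: "adverse events (AEs) or SAEs related to IMPs are used for safety evaluation".
- **Data collection, management and monitoring**: "During the whole study, all AEs (new incurrence symptoms or diseases, abnormal vital signs, clinically significant abnormal laboratory examination) should be recorded in CRF". Each event also goes on a report form "which includes start time, duration, severity, and relationship with IMP etc". For annual reporting, "all AEs and SAEs are required to be reported to the Department of Health".
- **Statistical analysis**: the main safety analysis is "analysis of the incidence of adverse events between groups and the incidence of abnormal laboratory data before and after treatment between groups". Relatedness is not mentioned.

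The **Blinding** section adds that "all the Chinese medicine practitioners, research assistants and participants are ignorant of the treatment assignments", so the site staff who judge relatedness do so without knowing the arm.

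**The concern.** The outcome definition is narrower than both the collection rule and the analysis rule. An analyst could apply the planned incidence comparison to the outcome as defined and count related events only. Another could count every recorded event. Each could claim to follow the protocol, and the article does not settle the choice in advance.

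The choice matters because the placebo arm already provides what is needed to judge causation. Comparing all events between randomised arms does not require anyone to decide, case by case, whether the drug was responsible. A filter on relatedness makes the comparison depend on those individual judgements. Being blinded, they should not favour an arm knowingly, but they can be wrong. A drug effect that resembles a common background complaint is the kind most easily put down to something else.

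**Working it through.** **1. The statements side by side**

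| Section | Events covered | Role of relatedness |
|---|---|---|
| Safety outcome | AEs or SAEs related to study drug | Condition for counting |
| Data collection | All AEs | A field on the form |
| Regulatory reporting (same section) | All AEs and SAEs | None |
| Statistical analysis | AE incidence by group; abnormal laboratory data by group | None |

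The Safety outcome and Data collection sections give nearly the same list of event types (new symptoms or diseases, abnormal vital signs, significant laboratory findings). They describe the same kind of data and differ in the relatedness condition.

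**2. The alternative grammar**

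The relatedness phrase could attach to SAEs alone. Non-serious events would then count whatever their cause, and serious events only if attributed to the drug. That still conflicts with the other sections, and it filters the most important events.

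**3. What does not pass through the filter**

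- Abnormal laboratory data have their own between-group comparison in Statistical analysis, so a liver-enzyme rise would still be compared.
- Worsening bowel symptoms are captured by the GAI (scores 0–2), the symptom diaries and the IBS-SSS.

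What remains exposed is mainly other clinical AEs and SAEs.

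**4. Sample size, for the arm size only**

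The article gives no safety power and no AE rate. Its one design figure reproduces if the 32% reported for the western medicine group is taken as the placebo rate (an assumption), with a 15-point difference, two-sided 5% and 80% power:

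n = [1.96·√(2·0.395·0.605) + 0.8416·√(0.32·0.68 + 0.47·0.53)]² / 0.15² = 165.6, so 166 per group.

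166 / 0.85 = 195.3, so 196 per arm and 392 in total. This point does not alter that figure.

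**5. What the restriction could do to a comparison of AE incidence**

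n = 196 per arm; two-sided 5%, the level that Statistical analysis gives for comparisons other than the primary outcome. All event rates and attribution shares are assumptions.

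Power = Φ[(d − 1.96·SE₀)/SE₁], with SE₀ = √(2p̄(1−p̄)/n) and SE₁ = √{[p₀(1−p₀) + p₁(1−p₁)]/n}.

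| Events counted (placebo v active) | d | SE₀ | SE₁ | Power |
|---|---|---|---|---|
| All events: 5% v 12% | 0.070 | 0.0282 | 0.0279 | 0.70 |
| Half of all events kept in each arm: 2.5% v 6% | 0.035 | 0.0204 | 0.0203 | 0.40 |
| Half the background and 80% of the excess kept: 2.5% v (2.5 + 0.8×7) = 8.1% | 0.056 | 0.0226 | 0.0225 | 0.70 |
| Half the background and all of the excess kept: 2.5% v 9.5% | 0.070 | 0.0240 | 0.0237 | 0.83 |

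For the first row: (0.070 − 1.96×0.0282)/0.0279 ≈ 0.53, and Φ(0.53) = 0.70.

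Other assumed rates, with the same share of events kept in both arms:

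| Share kept | 10% v 20%: excess, power | 20% v 30%: excess, power |
|---|---|---|
| 1 | 10 points, 0.79 | 10 points, 0.63 |
| 0.75 | 7.5 points, 0.65 | 7.5 points, 0.48 |
| 0.5 | 5 points, 0.47 | 5 points, 0.32 |
| 0.25 | 2.5 points, 0.26 | 2.5 points, 0.17 |

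If attribution is uninformative, the filter shrinks both the excess and the power. If it removes background and keeps drug effects, power holds or rises. The documents do not show which case applies.

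**The case against.** The strongest reply is that the section that actually specifies the analysis carries no restriction. It compares adverse event incidence between groups, all events are collected, and no sentence says that unrelated events will be dropped. On this view the outcome wording is a loose phrase in a condensed article, and the SAP, cited as Additional file 3 and not shown here, may name the event set. Much of this stands. A reader might infer from the Safety outcome sentence that the settled plan is to analyse drug-related events only; the documents do not support that, because Statistical analysis says otherwise.

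A reader might also infer that a liver-enzyme rise or worsening diarrhoea would vanish from the comparison if judged unrelated. That is not supported either, since both are compared by other routes.

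Thirdly, the power argument is not one-sided. A loss follows if attribution discards drug-caused and background events equally, but accurate attribution could raise power. That stands too, so a loss of power is possible rather than shown.

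What the reply does not remove is the contradiction. The only definition of the safety outcome contains a condition that the collection and analysis sections lack, and no rule of precedence is given. Clear wording in the SAP would settle the analysis but leave the article's outcome definition at odds with it.

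**Conclusion.** The inconsistency is real and lies in what the article states, not in what it leaves out. The outcome definition limits safety to drug-related events, while the collection and analysis text does not. If the definition governs, unattributed clinical AEs and SAEs drop out of the between-arm comparison, and an excess of harm could be hidden or distorted.

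The size is unknown, because no AE rates and no information on attribution accuracy are given. In the 5% v 12% illustration, power moves from 0.70 to anywhere between 0.40 and 0.83. The case for counting all events therefore does not rest on a certain loss of power. It rests on the comparison being valid whether or not the individual judgements are right.

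The primary outcome, the sample size and the efficacy error rate are unaffected. Because all AEs are to be recorded, the matter can be settled in the analysis without new data.

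**What to change.** Amend the Safety outcome section so that the outcome is all AEs and SAEs, whatever their judged relationship to study drug, compared between the arms as Statistical analysis already plans. Show the events judged related to study drug as a subset beside the full comparison. Check that the SAP names the same event set.

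Follow-up ended in February 2021 by the article's own account, so the event set should be fixed in writing before the treatment code is opened, if that is still possible.

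The cost is one reworded sentence and one more table. The visible downside is a higher reported AE incidence in both arms, since background complaints will be counted. Choices such as the effect measure and the safety population are ordinary SAP content and are not part of this point.

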### Quality control and assurance

Firstly, all investigators will be required to complete the TRREE on-line training programme on the ethics and regulation of health research involving human participants (https://elearning.trree.org/) and get the online certification of Good Clinical Practice (GCP) before the start of the study. Secondly, all investigators will study the details of the protocol and investigator’s brochure together at the research centre of Hong Kong Baptist University. If there are any modifications, investigator will also study the revision of the protocol and the investigator’s brochure in time. Thirdly, a regular monthly meeting will be held to report the study progress to principal investigators (i.e., recruitment, compliance, adverse events, etc.), assess the investigators’ activities (i.e., data collection, data entry, compliance with the protocol and investigator’s brochure, etc.), discuss and solve the problems (if any). In general, the meeting will be conducted at the office of Hong Kong Baptist University.

In addition, investigators are required to explain details of clinical trial to participants and obtain informed consent. Investigators should also let participants to be fully informed of the significance of trial and importance of medication. For participants with low compliance, investigators should follow the participant in time and record the reasons in details.

### Data collection, management and monitoring

All data will be collected through patient diaries, questionnaires, and CRFs. All enrolled participants have to record their abdominal pain, stool frequency, stool consistency in a paper-based patient diary throughout 18 weeks of study. At each visit, participants will be required to return the diaries and complete some questionnaires, including the GAI questionnaire, the IBS-QoL questionnaire, and the IBS-SSS questionnaire. Chinese medicine practitioners and study coordinators have to fill in the CRFs to record relevant information, such as blood pressure, the changes of TCM Pattern, and compliance/noncompliance with research medication and concomitant conventional maintenance therapy, etc. These data collected in visit 2 will be the baseline data. All personal information of participants will be kept confidential. The Research Electronic Data Capture (REDCap) [29, 30] will be used to collect and manage all participants’ data by researchers. All centers have corresponding personnel to input the data timely. The researchers with authorized accounts can log in and browse the data. All raw data collected by patient diaries, questionnaires, and CRFs could be shared based on the request and special approval from the team. During the whole study, all AEs (new incurrence symptoms or diseases, abnormal vital signs, clinically significant abnormal laboratory examination) should be recorded in CRF and investigators are also required to fill in the relevant information in the “Adverse Event Report Form”, which includes start time, duration, severity, and relationship with IMP etc. Once there is an AE which results in hypersensitivity towards research medication or significant abnormality on liver or renal function, investigators can suspend or terminate the IMP, and report to principal investigators in time. If there are any SAEs, investigators should fill in the “Serious Adverse Event Report Form” with signature and report to the Research Ethics Committee within 24 h. Also, all AEs and SAEs are required to be reported to the Department of Health of Hong Kong Special Administrative Region every year. The trial document will be kept for 7 years after the completion of the trial. The Research Ethics Committee of Hong Kong Baptist University and the Department of Health of Hong Kong Special Administrative Region play a role to monitor the data. The principal investigators need to submit the progress reports to the Research Ethics Committee of Hong Kong Baptist University and the Department of Health of Hong Kong Special Administrative Region every year, and to the funding agency Innovative Technology Commission of the Government of Hong Kong Special Administrative Region at every 6 months.

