### Primary outcome

The primary outcome is the improvement rate on the global assessment of improvement (GAI) score at week 10, same as the previous small scale study [16]. The participants will be asked to give a global assessment of their IBS symptoms at visit 3, 4 and 5 with the question “In the past 7 days, compared with your IBS symptoms before you started the trial, are you now: substantially worse, moderately worse, slightly worse, no change, slightly improved, moderately improved, or substantially improved? [25]’’ The global symptom improvement will be evaluated by scales (substantially worse = 0, moderately worse = 1, slightly worse = 2, no change = 3, slightly improved = 4, moderately improved = 5, substantially improved = 6). The 0–2 score, 3 score and 4–6 score represent worsen, no change and improvement, respectively. Improvement rate of GAI is defined as the proportion of participants with improvement (in scores of 4 or greater).

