### Secondary outcomes

#### IBS symptoms

IBS symptoms, including abdominal pain (with scores from 0 to 10 representing none to most severe), stool frequency and stool consistency will be recorded by participants in a diary throughout 18 weeks of study. Investigators will grade each symptom by cardinal symptoms evaluation quantitation scale (None = 0, Mild = 1, Moderate = 2, Severe = 3) shown in Additional file 3: Table S1. The changes of these IBS symptoms before and after the treatment will be used for efficacy evaluation. The details are as below:i.Pain responder rate in daily worst abdominal pain scores: According to the guidance of the U.S. FDA, pain responder is defined as that participant who meets the daily pain response criteria for at least 50% of the days with diary entries during the observational period of interest. Daily pain response is defined as the ≥ 30% decrease in the worst abdominal pain scores in the past 24 h compared to baseline (average of daily worst abdominal pain the 2-week prior to randomization). Pain score is ranked from 0 to 10 representing none to the most severe [26].ii.Stool consistency responder rate in daily stool consistency scores: Stool consistency responder is defined as that participant who meets daily stool consistency response criterion (i.e., score of 1, 2, 3, or 4 or absence of bowel movement if accompanied by ≥ 30% decrease in worst abdominal pain scores compared to baseline pain) for at least 50% of days with diary entries during the observational period of interest. Bristol stool scale is defined as 7-point Scale in which a score of 1 = separate hard lumps, 2 = sausage shaped but lumpy, 3 = sausage-like with cracks on the surface, 4 = sausage-like but smooth and soft, 5 = soft blobs with clear cut edges, 6 = fluffy pieces with ragged edges, and 7 = watery with no solid pieces [26].iii.Improvement rate and efficacy rate*:* The standards of efficacy assessment of single symptom are as follows: (a) Excellent: symptoms disappearing; (b) Effective: symptom score decreased ≥ 2 points; (c) Helpful: symptom score decreased 1 point; (d) Invalid: no change in symptom score. Improvement rate is defined as the proportion of participants in excellent, effective and helpful. Comprehensive efficacy judgement standard of cardinal symptoms is calculated by “(total scoring of prior treatment − total scoring of post treatment)/total scoring of prior treatment × 100%”. Clinical remission is defined as symptom disappearing, symptom improvement (≥ 80%), helpful (between 50 and 80%), invalid (< 50%). Total effective rate is defined as the proportion of participants with clinical remission and symptom improvement [23].

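### The stated adverse event lists do not name worsening of baseline symptoms, and no efficacy rate counts participants made worse, so aggravated pain or diarrhoea has no explicit place in the safety comparison

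*Protocol article*

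**What the plan says.** Assessing safety is the second of the two objectives. Under Data collection, management and monitoring, "all AEs (new incurrence symptoms or diseases, abnormal vital signs, clinically significant abnormal laboratory examination) should be recorded in CRF". The Safety outcome section says that "adverse events (AEs) or SAEs related to IMPs are used for safety evaluation, including new incurrence symptoms or diseases, abnormal vital signs", and adds laboratory abnormalities of kidney or liver function. Severity is graded by CTCAE v4.0. The Statistical analysis section rests safety mainly on the incidence of adverse events and of abnormal laboratory results in each group.

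On the efficacy side, the GAI is asked at visits 3, 4 and 5 (weeks 6, 10 and 18). The Primary outcome section separates three bands: "The 0–2 score, 3 score and 4–6 score represent worsen, no change and improvement, respectively". The rate that is analysed is two-way: "Improvement rate of GAI is defined as the proportion of participants with improvement (in scores of 4 or greater").

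Under IBS symptoms, pain and stool consistency are analysed as responder or not. The lowest level of the single-symptom scale is "d) Invalid: no change in symptom score". The comprehensive scale runs "symptom improvement (≥ 80%), helpful (between 50 and 80%), invalid (< 50"%). The TCM pattern section puts exacerbation in the same lowest class as lack of improvement. IBS-QoL and IBS-SSS are analysed as differences in score, and repeated outcomes as follow-up minus baseline.

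**The concern.** The Rome IV and LSSD criteria under Inclusion and exclusion criteria require abdominal pain and diarrhoea at entry. For all 392 participants, worse pain or worse diarrhoea is therefore an aggravation and not a new symptom. A site that follows the recording rule literally has no instruction to enter it as an adverse event, and what is not entered cannot reach the incidence comparison.

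Aggravation of gut symptoms is a plausible harm of an oral product meant to act on bowel function. If the granules help some participants and aggravate others, the improvement rate shows the help, and no stated rate shows how many got worse. The adverse event comparison could then look more even between the arms than the participants' own answers do, although those answers are collected.

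**Working it through.** **1. Where a participant whose symptoms worsen would appear**

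| Measure (section) | Treatment of worsening |
|---|---|
| Adverse event recording (Data collection, management and monitoring) | Not named in the list |
| Adverse events for evaluation (Safety outcome) | Not named; list introduced as non-exhaustive |
| GAI improvement rate (Primary outcome) | Scores 0–2 pooled with 3 |
| Pain and stool responder rates (IBS symptoms) | Non-responder, as if unchanged |
| Single-symptom scale (IBS symptoms) | No category |
| Comprehensive scale (IBS symptoms) | Any change below 50%, including negative change, in the lowest class |
| TCM pattern scale (TCM pattern) | Pooled with no improvement |
| IBS-SSS, IBS-QoL, change from baseline | Direction kept, as a mean |

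Only the last row keeps the sign. It contributes to a group average, in which gains in some participants offset losses in others.

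**2. The single-symptom scale is incomplete as stated**

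Each symptom is graded 0 to 3. With a symptom present at baseline (grade 1, 2 or 3) and four possible later grades, there are 3 × 4 = 12 before-and-after pairs. Three of them are increases: 1 to 2, 1 to 3, and 2 to 3. None of the four levels covers these three pairs. A participant at grade 3 cannot register an increase at all, so a worse category would still miss aggravation in those who start at the top of the scale.

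**3. What an excess of worsening could look like (assumed counts)**

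The documents give no rate of worsening, so the counts below are assumptions. The only planning figure used is 196 per arm, which follows from the stated 166 per group and 15% drop-out: 166 / (1 − 0.15) = 195.3, rounded up to 196.

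The test is a two-proportion chi-square without continuity correction: χ² = N(ad − bc)² / (n₁ n₂ m₁ m₂). Here a and c are the numbers worse in each arm, b and d the numbers not worse, n₁ and n₂ the arm sizes, and m₁ and m₂ the total worse and not worse.

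- 20 v 6 worse: 20/196 = 10.2% and 6/196 = 3.1%, a difference of 14/196 = 7.1 points. χ² = 392 × (20 × 190 − 176 × 6)² / (196 × 196 × 26 × 366) = 392 × 2744² / 365,566,656 = 8.07, p = 0.0045.
- 12 v 6 worse: 12/196 = 6.1% and 6/196 = 3.1%, a difference of 6/196 = 3.1 points. χ² = 392 × (12 × 190 − 184 × 6)² / (196 × 196 × 18 × 374) = 392 × 1176² / 258,616,512 = 2.10, p = 0.15.

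In the first case the excess is 14 people. If they move from GAI 3 to GAI 0–2, the number scoring 4 or more does not change, so the improvement rate does not change either. Whether any of them appears in the adverse event table depends on how the site read the definition.

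**The case against.** A reader might infer that adverse events are confined to new symptoms, or that worsening is counted nowhere as harm. The article does not support either reading.

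- Both lists also contain vital signs and laboratory findings, so the definition is not limited to new symptoms or diseases.
- The Safety outcome section opens its list with a word that leaves it open. The parenthesis in the recording rule may be the same shorthand. Neither place excludes worsening.
- The full protocol, the adverse event forms and the SAP (Additional file 3) are not shown and may say more. Worsening that met the criteria for a serious event would presumably be reported as such, although the article does not define a serious event.
- The GAI has its own band for worsening. IBS-SSS, IBS-QoL and the change-from-baseline analyses keep direction, so aggravation in the active arm would reduce its mean benefit. Keeping deterioration of the disease under study within efficacy is a legitimate design choice.
- Bloating and passing gas are secondary LSSD signs, of which only two or more are needed. They are not universal at baseline, and their onset in someone without them would be a new symptom. The gap applies to everyone only for pain and diarrhoea.
- The single-symptom levels come from a cited guideline, and the counts in the working are illustrative.

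All of this stands and limits the claim. It does not remove the point. The article does not leave the definition to another file: it states the list twice, and both times worsening is not named. The single-symptom scale as printed has no place for a score that rises. The measures that keep direction give means and not a number of people made worse. A worse level would not alter the guideline's improvement rate, which counts only the three improved levels.

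**Conclusion.** The point holds in a limited form. As written, the adverse event lists give aggravation of baseline pain or diarrhoea no explicit route into the safety comparison, and no stated efficacy rate reports participants made worse separately from those unchanged. The data that would show it are collected and are analysed as efficacy.

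The size cannot be estimated from the documents. The illustration shows only that, under assumed counts, a statistically clear excess of 7.1 points is compatible with an unchanged improvement rate. Any effect on the adverse event comparison rests on the assumption that sites applied the recording rule literally and that no unseen document told them otherwise. The primary analysis and the sample size are unaffected.

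**What to change.** 1. Report as a safety result the proportion with GAI 0–2 by arm at weeks 6, 10 and 18, with the number answering at each visit as the denominator. The question covers the past 7 days, so the table will miss worsening that resolved between visits. If the treatment code has already been broken when the table is added, label it post hoc.
2. Add a worse category (score increased by at least 1 point) to the single-symptom scale, and note that participants at grade 3 at baseline cannot enter it.
3. Amend the adverse event definition, in both sections, to include worsening of conditions present at baseline. The Trial status section reports that the last follow-up was on 17 February 2021, so new wording cannot change how events were recorded. The practical alternative is to state whether worsening of baseline IBS symptoms was recorded as an adverse event and, if it was not, to report this as a limitation of the safety data.

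The cost is one extra table, one extra scale level and a short statement, all from data already collected. The downside is a possibly less favourable safety profile.
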